### Sample size/recruitment

The primary endpoint is time to first passing flatus, which is defined as hours between end of operation and first flatus after operation. To calculate the sample size, a literature review was performed on acupuncture and its effect on bowel motility after laparoscopic surgery. The most similar study to this trial is that of Yu et al. [15]. They measured flatus time after laparoscopic cholecystectomy in an electric acupuncture group (n = 30), analgesia-pumper group (n = 30), and a control group (n = 30). The flatus time was shorter in the electric acupuncture group as compared with the other two groups [(14.77 ± 4.99) hours versus (18.50 ± 4.22) hours, *P* < 0.01; (14.77 ± 4.99) hours versus (18.17 ± 4.69) hours, *P* < 0.05].

For the AcuLap trial, the estimated number of participants to detect a minimum difference of time to first flatus with 80 % power, 5 % significance, and 10 % drop rate is 29 × 3 groups = 87 patients.

### Methods: assignment of interventions

#### Allocation

Allocation sequence will be generated using block randomization with StatsDirect 3 software by a randomizing person at the study center. After obtaining an informed consent from an eligible patient, the recruiter will be given a treatment code assigned to the patient from the centrally generated allocation sequence to which access is restricted for the recruiter.

#### Blinding

Two of the treatment codes are electroacupuncture and sham electroacupuncture; and the other code is control. Patients, physicians/nurses, and data analyzers are blinded between electroacupuncture and sham electroacupuncture. Only oriental medicine doctors who perform acupuncture know which treatment code corresponds to which procedure between two interventions.

The control group cannot be blinded.

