#### Secondary outcomes

Secondary outcomes include postoperative pain, analgesics, nausea/vomiting, bowel motility, time to tolerable diet, complications, hospital stay, readmission rates, time to recovery, quality of life, medical costs, and protocol failure rate.

Postoperative pain will be checked regularly three times a day and will be recorded using the visual analog scale.

Intravenous analgesic injections will be counted daily.

Nausea and vomiting will be counted daily.

Bowel motility will be checked regularly three times a day, by attending surgeons. Bowel sound will be counted in a minute by auscultation.

Postoperative complications will be checked according to Accordion Severity Classification of Postoperative Complications [13].

Time to recovery is defined as time to ambulate and perform self-care by patient himself or herself.

Discharge is recommended when the patient meets ***discharge criteria*** as follows:Controllable pain with analgesicsNo nausea/vomitingPassing flatus or fecesToleration of soft dietMobilization (independent walking) and self-careControlled complications less than moderate by Accordion system (Table 1)

**Table 1 Tab1:** Accordion severity classification of postoperative complications: expanded classification [13]

1. Mild	Requires only minor invasive procedures that can be done at the bedside such as insertion of intravenous lines, urinary catheters, and nasogastric tubes, and drainage of wound infections. Physiotherapy and the following drugs are allowed: antiemetics, antipyretics, analgesics, diuretics, electrolytes, and physiotherapy.
2. Moderate	Requires pharmacologic treatment with drugs other than those allowed for minor complications, for instance, antibiotics. Blood transfusions and total parenteral nutrition are also included.
3. Severe	Invasive procedure without general anesthesia. Requires management by an endoscopic, interventional procedure or re-operation^a^ without general anesthesia.
4. Severe	Operation under general anesthesia. Requires management by an operation under general anesthesia.
5. Severe	Organ system failure.^b^
6. Death	Postoperative death.

^a^An example would be a wound re-exploration under conscious sedation and/or local anesthetic

^b^Such complications would normally be managed in an increased acuity setting, but in some cases patients with complications of lower severity might also be admitted to an ICU

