#### Consent/confidentiality

Attending surgeons will obtain written informed consent from all trial participants before inclusion. All collected data will be kept confidential at all times.

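### One treatment code shared by each arm is handed to the recruiter, so learning one needled patient's arm would reveal both needle arms (at most 58 of 87 patients)

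*Protocol article*

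**What the plan says.** All places are in the protocol article.

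- **Codes (Blinding).** "Two of the treatment codes are electroacupuncture and sham electroacupuncture; and the other code is control". On who holds the key: "Only oriental medicine doctors who perform acupuncture know which treatment code corresponds to which procedure between two interventions".
- **Release (Allocation).** After consent, "the recruiter will be given a treatment code assigned to the patient from the centrally generated allocation sequence". The stated safeguard concerns the list: "allocation sequence to which access is restricted for the recruiter". Nothing is said about masking codes already issued.
- **Who takes consent (Consent/confidentiality).** "Attending surgeons will obtain written informed consent from all trial participants before inclusion".
- **Who must be blind (Blinding).** "Patients, physicians/nurses, and data analyzers are blinded between electroacupuncture and sham electroacupuncture". The third arm is open: "The control group cannot be blinded".
- **Who assesses (Secondary outcomes).** "Bowel motility will be checked regularly three times a day, by attending surgeons".
- **Timing (Participant timeline and Table 2).** Patients are enrolled before surgery and allocated after enrolment. Table 2 puts the allocation column ahead of the operation-day column.

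**The concern.** With one label per needle arm, the only secret is which of two labels means real current. That secret is common to all needled patients, so it can be lost for all of them at once. The person who receives the labels is probably among the staff the protocol wants to keep blind.

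The Discussion bases its claim of a true acupuncture effect on electroacupuncture versus sham, so masking between these two arms matters more than anywhere else in the design. An unmasked surgeon could be influenced when counting bowel sounds. Under Routine postoperative care, bowel sounds lead to sips of water and then soft diet, and tolerating soft diet is one of the discharge criteria. The effect could therefore reach bowel motility, time to diet and hospital stay.

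A second consequence needs no leak. The control code is not secret. A recruiter who holds the code before surgery knows whether the patient will be needled while eligibility can still change.

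**Working it through.** **1. Arm size.** The Sample size section gives 29 × 3 = 87. From the cited cholecystectomy study the difference is 18.50 − 14.77 = 3.73 h, and the pooled SD is √((4.99² + 4.22²)/2) = 4.62 h. With two-sided 5% (sidedness is not stated, so this is assumed) and 80% power, the t-based calculation gives 26 per arm. Then 26/(1 − 0.10) = 28.9, which rounds up to 29. The figure is reproduced, and this point does not affect it.

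**2. Number of codes.** The Blinding section counts two needle codes and, in the singular, one other code for control. It then describes one correspondence between codes and procedures. Two arms and two labels give two possible keys, so one needled patient whose arm is known settles the key.

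**3. Patients exposed by one leak.**

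| Who knows which codes | Needled patients exposed |
|---|---|
| One person knows all codes | 2 × 29 = 58 of 87 (67%) |
| Each of three surgeons knows only their own, evenly split (assumed) | 58/3 ≈ 19 of 87 (22%) |
| A unique number per patient | 1 |

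**4. How likely a leak is.** The documents give no rate, so this is illustration only. Suppose each of 58 needled patients independently reveals the arm with probability p. The chance of at least one leak is 1 − (1 − p)^58: 44% for p = 1%, 69% for p = 2% and 95% for p = 5%. Some route exists: the real device delivers current, while in the sham the internal wire is cut and the patient only hears a sound.

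**5. Timing against the exclusions.** The Exclusion criteria include several that are settled, or may be settled, in the operating room: conversion to open surgery, combined surgery including ileocecectomy, another disease found at operation, and a need for fasting based on operative findings. By the order in Participant timeline and Table 2, the code has been issued by then. If the holder is also judging those criteria, the judgement is made knowing needle versus control.

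**6. Who the recruiter is.** Allocation says recruiter. Consent/confidentiality says attending surgeons take every consent, and the code follows consent. Together these point to a surgeon, but no sentence says so outright.

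**The case against.** **The codes may be patient-specific.** The Allocation wording, read alone, fits individual codes that map to arms, and an article may leave coding detail to the full protocol. This is possible, but the Blinding wording does not fit it well. It is met by asking for that section to be reworded if so.

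**The figure of 58 is a ceiling.** This stands. It needs one person who knows every needle code. Later unmasking also cannot bias in-hospital assessments already recorded for discharged patients, so the practical harm falls on patients on the ward or still to come.

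**A report of feeling current is a clue, not a disclosure.** This also stands. Sham patients may report sensations too, and unique numbers would not remove the clue for that patient. They only stop it carrying over to others.

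**Patient blinding does not depend on the codes.** Correct: it rests on the sham device and matching sound. A reader might infer that the primary outcome is compromised. The documents do not support that, because nothing says surgeons judge time to first flatus. The surgeon-assessed measure named is bowel sounds, which is secondary.

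**A reader might infer that visible codes make the block sequence predictable.** The documents do not establish this. Block size is not given, and an article may omit it. For assumed blocks of 3 to 12, the next code is guessed correctly 61% down to 51% of the time, against 33% by chance, but only if one recruiter sees every earlier code. If each of three surgeons sees only their own patients' codes, the figure is about 36%. Before any leak, a guessed needle code is only a label and cannot steer enrolment between electroacupuncture and sham. Needle versus control is visible anyway because control is open. With block size known and no codes seen, it is already certain for about 44% (block 3) to 17% (block 12) of patients, and renumbering does not remove that.

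**Conclusion.** The masking weakness holds on the plain reading of the Blinding and Allocation sections. A single leak would reveal both needle arms to anyone holding codes, for at most 58 of 87 patients and about 19 if codes are split evenly among three surgeons. Early release also shows needle versus control while intraoperative exclusions are undecided.

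This rests on three things: that the code is shared within each arm (the natural reading), that the recruiter is an attending surgeon (an inference from two sections), and that allocation precedes surgery (the order in Table 2). It is a weakness in a stated procedure; it does not show that the blind has failed. No claim is made about predictable blocks, the primary outcome or the sample size. The change is worth making because it is cheap and protects the contrast on which the Discussion relies.

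**What to change.** - Give each patient a unique randomization number that does not show the arm.
- Keep the number-to-arm list with the randomizing person and open it only to the acupuncturists.
- Give the recruiter only the number at consent.
- Tell the ward whether the patient is to be needled only after the operation, once the intraoperative exclusions are settled.
- If patient-specific codes are already in use, reword the Blinding section to say so. The timing of release still needs stating.

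The cost is a renumbered allocation list and a short amendment. The allocation order, treatments and sample size do not change. The small downside is that the acupuncturist must look up each number. The trial has been open since June 2015, so the change can protect only patients not yet randomized; codes already issued stay shared.

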### Methods: data collection, management, and analysis

#### Data collection methods

All data will be collected using the daily assessment form and will be recorded in case record form, from operation day to discharge day (Table 3). Postoperatively, on the first visit to the outpatient clinic, a quality of life questionnaire (SF-36) will be filled in by the patient.

**Table 3 Tab3:** Daily assessment form: from operation day to discharge day

		Operation	POD1	POD2	POD3	POD4	POD5	…….	Discharge
Pain score (VAS)	1) Morning: ___								
	2) Mid-day: ___								
	3) Evening: ___								
IV analgesics	___/day								
Nausea/vomiting	Nausea: No/Yes(___/day) Vomiting: No/Yes(___/day)								
Bowel motility (bowel sound/minute)	1) Morning: __/min								
	2) Mid-day: __/min								
	3) Evening: __/min								
Intestinal passage	Flatus: Yes(___/day)/No								
	Stool: Yes(___/day)/No								
Tolerability to liquid	Yes/No								
Tolerability to soft diet	Yes/No								
Mobilization and self-care	Yes/No								
Postoperative complications (Accordion classification)	No/ 1/ 2/ 3/ 4/ 5								
Fulfillment of defined discharge criteria	___/total(5)								
Patient’s agreement to discharge	Yes/No								

*VAS* visual analogue scale, *POD* postoperative day

#### Statistical methods

Analysis of primary outcome:

Median of first flatus time will be analyzed by the Student’s *t*-test. *P* values less than 0.05 will be regarded as statistically significant.

Analysis of secondary outcomes:

Categorical data will be analyzed by the chi-square test or Fisher’s exact test. Continuous data will be analyzed by the unpaired *t*-test or Wilcoxon’s rank sum test. *P* values less than 0.05 will be regarded as statistically significant.

Missing data less than 5 % of the sample will be dropped. For missing data that amount to more than 5 %, analysis will be carried out with missing data imputation by the last observation carried forward and the maximum likelihood estimation method.

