### Participant timeline

Patient enrollment will be done before operation. After eligibility screen, an informed consent will be obtained at outpatient clinic, emergency department, or ward. After enrollment, random allocation will be performed using blocks. The interventions (electroacupuncture or sham electroacupuncture) will be given twice a day after operation, from operation day to postoperative day 2. All clinical outcome variables will be assessed from operation day until discharge day; except for quality of life, readmission, medical costs, and protocol failure, which will be assessed on the first visit day (postoperative day 7) after discharge (Table 2).

**Table 2 Tab2:** Time schedule of enrollment, interventions, and assessments

	Study period							
	Enrollment	Allocation	Post-allocation					Close-out
TIMEPOINT	-t_1_	0	t_0_	t_1_	t_2_	…	t_x_	t_x+1_
Enrollment:								
Eligibility screen	X							
Informed consent	X							
Allocation		X						
Interventions:								
Electroacupuncture			X	X	X			
Sham electroacupuncture			X	X	X			
Control								
Assessments:								
Passing flatus			X	X	X	X	X	
Postoperative pain			X	X	X	X	X	
Analgesics			X	X	X	X	X	
Nausea/vomiting			X	X	X	X	X	
Bowel motility			X	X	X	X	X	
Tolerability to diet			X	X	X	X	X	
Complications			X	X	X	X	X	
Time to recovery			X	X	X	X	X	
Fulfillment of defined discharge criteria			X	X	X	X	X	
Patient’s agreement to discharge			X	X	X	X	X	
Quality of life								X
Hospital stay								X
Readmission rate								X
Medical costs								X
Protocol failure rate								X

-t_1,_ time before operation; t_0_, operation day; t_1_-t_x_, postoperative day 1 to postoperative day *X* (= actual discharge day); t_x+1,_ the first visit day on outpatient clinic after discharge

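### The primary analysis names a median but tests it with Student's t-test, and has no suitable rule for patients whose first flatus is not observed before discharge

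*Protocol article*

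**What the plan says.** All locations are in the protocol article.

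- **Statistical methods**, primary outcome: "Median of first flatus time will be analyzed by the Student’s *t*-test". No rank-based or time-to-event method is named for it. For continuous secondary outcomes the same section allows either an unpaired t-test or Wilcoxon's rank sum test.
- **Sample size/recruitment**: the endpoint is "defined as hours between end of operation and first flatus after operation", so it is a time to an event. The size is justified from one cholecystectomy study's flatus times given as value ± spread, and the result is stated "with 80 % power, 5 % significance, and 10 % drop rate is 29 × 3 groups = 87 patients".
- **Participant timeline**: "All clinical outcome variables will be assessed from operation day until discharge day", with a few named exceptions that do not include flatus. Table 2 likewise shows no flatus assessment at the close-out visit.
- **Secondary outcomes**, discharge criteria: discharge is recommended once several conditions are met. The bowel condition is satisfied by either flatus or feces.
- **Statistical methods**, missing data: below 5 % of the sample, missing values are dropped. Above 5 %, they are handled by last observation carried forward (LOCF) and maximum likelihood.
- **Trial design**: analysis follows the intention-to-treat principle.

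**The concern.** The sentence on the primary outcome contradicts itself. A t-test yields a p-value and an interval for a difference in means and gives neither for a median. It is therefore not fixed whether the trial will be judged on mean or median flatus time, and for a skewed recovery time the two can differ. If that choice is left until the data are seen, the single primary comparison loses its pre-specified status.

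The second part follows from the endpoint. A patient discharged after passing feces but not flatus contributes only the information that first flatus came later than the last assessment. A t-test cannot use that, and the missing-data rule treats it as an absent value. Dropping the patient sits badly with intention to treat. LOCF needs an earlier value of the same quantity, and a first-event time has none.

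**Working it through.** **1. What the sample size was built on.** Inputs from Sample size/recruitment: 14.77 ± 4.99 h against 18.50 ± 4.22 h, 80 % power, 5 % significance, 10 % dropout. Two assumptions: the ± figures are SDs around means, and the test is two-sided.

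- Difference d = 18.50 − 14.77 = 3.73 h.
- Pooled SD = √[(4.99² + 4.22²)/2] = 4.62 h, so d/SD = 0.807.
- Normal approximation: n = 2(1.960 + 0.842)² × 4.62²/3.73² = 24.1, so 25 per arm, and 25/0.90 rounds up to 28.
- Noncentral t: n = 25.09, so 26 per arm (power 0.814), and 26/0.90 = 28.9, so **29**.

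The stated 29 is reproduced exactly as a t-test on means. The study's other contrast (3.40 h, pooled SD 4.84 h) needs 33 evaluable and 37 enrolled per arm two-sided, and gives 29 only one-sided. That too is a comparison of means. No median enters the planning.

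**2. Can a flatus time be unobserved?** Flatus assessment ends at discharge, and discharge may follow feces without flatus. The two rules together allow it. The article gives no frequency. It should be low, since most patients will meet the bowel criterion through flatus.

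**3. What a change of test costs or gains.** Simulation with 26 evaluable per arm, the means and SDs of step 1, normal data, two-sided 5 %. The outlier share q and its size (extra ileus of mean 24 h, SD 12 h, in both arms) are assumptions, because the documents give no such rate.

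| q in each arm | t-test | Wilcoxon |
|---|---|---|
| 0 | 81 % | 79 % |
| 2 % | about 65 % | about 75 % |
| 5 % | about 48 % | about 71 % |
| 10 % | about 33 % | about 63 % |

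These outliers are added on top of the cited SDs. The total SD becomes √[4.62² + q(24² + 12²) − (24q)²]. At q = 5 % this is √(21.4 + 36.0 − 1.4) = 7.5 h, and at q = 10 % it is √(21.4 + 72.0 − 5.8) = 9.4 h, about twice the planning value. If the same contaminated shape is rescaled so that each arm keeps its cited SD, the t-test keeps about 80 % and Wilcoxon rises to about 98 % at q = 5 %.

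With no true difference, the t-test rejects in at most about 5 % of runs, with or without outliers. No censoring was simulated, so these figures bear on the choice between means and ranks and not on the unobserved times.

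**The case against.** The strongest reply is that one word is wrong. Sample size and test agree on means, so replacing the median by the mean would end the contradiction without touching the test. That is correct as far as it goes, but it leaves the unobserved flatus times under the drop-or-LOCF rule.

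A second reply is that a rank test does not test medians either. That also stands. Wilcoxon and its censored-data forms compare whole distributions, and their p-value corresponds to a difference in medians only under a pure shift. The reworded plan must say so.

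Third, a reader might infer that the t-test discards the slowest patients. The documents do not show this. Someone discharged on the feces route has also tolerated a soft diet and walked independently, while slow patients remain in hospital and under observation. For the same reason, censoring at discharge is not plainly independent of bowel recovery, which calls for a sensitivity analysis.

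Fourth, a reader might infer that the trial will lose most of its power to one or two outliers. That rests on a tail the documents do not give. Under the model above, exactly one such patient per arm leaves the t-test about 48 %, and there is no collapse if the cited SDs already contain such patients. The article excludes patients who need postoperative fasting and expects fast recovery in most.

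**Conclusion.** The point holds in a limited form. Two things follow from the text without any assumption about rates: the primary summary and the primary test do not match, and the stated missing-data rule is unsuitable for a first-event time not reached by discharge. This is a faulty statement in the protocol and not a detail left to an analysis plan.

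The number of patients affected by the second fault is unknown and probably small. The power argument is secondary. A rank-based test loses about 2 points if the data are exactly normal. It was the more powerful test in every contaminated scenario in step 3, but the size of the advantage depends on the assumed tail. A reader should not conclude that the t-test is invalid here, since its type I error is not shown to be inflated, or that the planned 29 per group is wrong for a comparison of means.

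**What to change.** Reword the primary-outcome paragraph of Statistical methods before any unblinded look at the data:

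- **Test:** a rank-based primary test. This is the Wilcoxon rank sum test, already named for secondary outcomes, or its Gehan or Peto-Prentice form when any flatus time is unobserved. State that it compares the distributions of flatus time and is not a test of medians as such. A plain log-rank test is a poor substitute: under the normal model above with no outliers its power is about 64 %.
- **Unobserved times:** censor patients without flatus at their last flatus assessment, and exempt them explicitly from the drop-or-LOCF rule. As a sensitivity analysis, rank them after all observed times.
- **Estimates:** Kaplan-Meier medians with 95 % CI by arm. Give the mean difference with 95 % CI as supportive, because the sample size was built on means.

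The cost is a change of wording and about 2 points of power with exactly normal data (81 % to 79 % at 26 evaluable per arm). No further patients or assessments are needed.

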## Methods/design

### Trial design

The AcuLap trial is a single-center, prospective randomized controlled trial with a three-arm, parallel-group design (Fig. 1). Data analysis will be performed according to the intention-to-treat principle.

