### Interventions

#### Study outline

Patients with appendicitis undergoing laparoscopic surgery are included and randomized into three groups: 1) electroacupuncture group, 2) sham acupuncture group, and 3) no acupuncture group. Patient allocation is performed by block randomization.

After laparoscopic appendectomy, routine postoperative care is equally given to all patients except for interventions (electroacupuncture or sham acupuncture). Clinical outcomes including postoperative pain score and bowel motility recovery are evaluated in each of the three groups during hospitalization. Quality of life and medical cost are evaluated after discharge.

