## Discussion

Garcia et al. reviewed 41 randomized controlled trials (RCTs) evaluating the efficacy of acupuncture for symptom management in patients with cancer [10]. Pain, nausea, and postoperative ileus were the most commonly studied symptoms. Among those RCTs, only one study, by Shen et al. [16], showed a positive conclusion for nausea with low risk of bias. For symptoms other than nausea, the efficacy of acupuncture remained undetermined because of the high risk of bias. Eleven RCTs on pain [17–27], 10 RCTs on nausea [24, 28–36], and 8 RCTs on ileus [17, 18, 23, 37–41] were identified as having high or unclear risk of bias and showed positive or negative conclusions for each symptom.

From the literature review, we concluded that acupuncture needs to be studied with a more sophisticated design to justify its unproven efficacy. The AcuLap trial aims to evaluate the postoperative effect of electroacupuncture on bowel motility recovery and pain relief in patients undergoing laparoscopic appendectomy. We anticipate that the trial will provide high-level evidence on the merits and/or demerits of electroacupuncture after laparoscopic surgery.

The strength of this study lies in proving the true effect of acupuncture on postoperative recovery by comparing patients receiving true acupuncture or sham acupuncture and a control group. If the true acupuncture group shows a better outcome compared to the sham group, the true effect of acupuncture can be justified on postsurgical patients. However, if the true acupuncture group fails to show a superior outcome to the sham group, even though the acupuncture group shows better recovery compared to the control group, a placebo effect of acupuncture should be considered. This is the first published protocol in English to investigate the efficacy of acupuncture on postoperative pain and ileus after laparoscopic appendectomy. We hope to share this protocol with any investigators who are interested in acupuncture and postsurgical recovery.

On the other hand, it is possible that the study may not reveal statistically significant positive or negative conclusions, because laparoscopic appendectomy is minimally invasive surgery, and most patients undergoing laparoscopic appendectomy show fast recovery after surgery. However, we hope to design our next study in other surgical procedures using the experiences from this study.

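### Three arms are analysed with a two-sample t-test at 0.05 and no named primary contrast, and the placebo reading ignores both sham v control and the EA–sham confidence interval

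*Protocol article*

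**What the plan says.** The trial is a "prospective randomized controlled trial with a three-arm, parallel-group design", with patients "randomized into three groups: 1) electroacupuncture group, 2) sham acupuncture group, and 3) no acupuncture group" (Study outline).

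For the primary outcome, Statistical methods states: "Median of first flatus time will be analyzed by the Student’s" t-test. For secondary outcomes: "Continuous data will be analyzed by the unpaired" t-test or a rank sum test. In both cases P "values less than 0.05 will be regarded as statistically significant". The section names no pair of arms, global test, order of testing or adjustment.

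Sample size/recruitment plans for "80 % power, 5 % significance, and 10 % drop rate is 29 × 3 groups = 87 patients". It does not say which contrast is powered or which difference was used. Its source study had EA, analgesia-pump and control arms, and no sham arm.

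The Discussion supplies the interpretation. On one outcome: "If the true acupuncture group shows a better outcome compared to the sham group, the true effect of acupuncture can be justified". If EA does not prove superior to sham, "even though the acupuncture group shows better recovery compared to the control group, a placebo effect of acupuncture should be considered". The Discussion also concedes that the trial may end without a significant conclusion either way.

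**The concern.** A Student's t-test compares two groups. With three arms it must be applied to one, two or three pairs, and the analysis section does not say which. The Discussion makes EA v sham the contrast that matters, but the section that fixes the analysis does not. An EA v control result at P<0.05 could therefore be reported as the primary finding without departing from Statistical methods. That comparison cannot be blinded, whereas EA v sham is blinded for patients and ward staff (Blinding).

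The placebo sentence is a separate weakness. It reasons from failure to show EA superior to sham. It does not ask how large an EA–sham difference the data still allow. It also does not use sham v control, the contrast that measures a placebo effect directly. Low power for EA v sham can produce the pattern even when EA has a real specific effect.

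**Working it through.** **Inputs.** Sample size/recruitment gives flatus times of 14.77 ± 4.99 h (EA) against 18.50 ± 4.22 h and 18.17 ± 4.69 h, with 80% power, 5% significance and 10% dropout. Two-sided testing is assumed because sidedness is not stated. The simulations assume normally distributed times.

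**1. The plan's own figure.** Formula: n = 2(1.96 + 0.842)² × SD² / difference².
- Difference 18.50 − 14.77 = 3.73 h; pooled SD = √[(4.99² + 4.22²)/2] = 4.62. Then n = 2 × 7.85 × 21.35 / 13.91 = 24.1, so 25. The t-based version gives 26, and 26/0.9 = 28.9, so **29 per arm**, as stated.
- Difference 18.17 − 14.77 = 3.40 h; pooled SD = 4.84. Then n = 2 × 7.85 × 23.45 / 11.56 = 31.8, so 32 (t-based 33). With dropout this is 36–37 per arm, which does not match.

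The 29 is therefore reproduced by one two-group comparison at an unadjusted 0.05, with 26 evaluable per arm. Nothing in it allows for more contrasts.

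**2. False-positive rate with all arms equal.** Treating the tests as independent gives 1 − 0.95³ = 14.3% for three pairs and 1 − 0.95² = 9.75% for two. The pairs share arms, so the true values are lower. Simulation with 26 per arm and 40,000 replicates gives:
- any of three pairs: 12.2%;
- either EA contrast, either direction: 9.1%;
- either EA contrast, in favour of EA: about 4.5%;
- EA v sham alone: 5% by construction.

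**3. How often the Discussion's placebo pattern appears.** The pattern is EA significantly better than control with EA not significantly better than sham. The share of the effect carried by sham is an assumption, because the article gives no EA–sham difference. Both source contrasts are shown, with 26 per arm and the comparator SD used for sham and control:

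| Sham share | 3.73 h: EA–sham power | 3.73 h: pattern | 3.40 h: EA–sham power | 3.40 h: pattern |
|---|---|---|---|---|
| 0 (inert) | 81% | 10% | 70% | 14% |
| 25% | 57% | 28% | 46% | 30% |
| 50% | 30% | 53% | 24% | 48% |

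With the pooled SD of 4.62 throughout, the 3.73 h patterns are 11%, 29–30% and 53%.

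**4. Precision of EA v sham.** The 95% CI half-width is t(50) × SD × √(2/26) = 2.009 × 4.62 × 0.277 = **2.6 h** (2.7 h with SD 4.84). An observed EA advantage just short of significance, about 2.5 h, would carry an interval from about 0 to about 5 h. That is no evidence that EA and sham are alike.

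**The case against.** The strongest reply is that the Discussion already settles the matter. It allows a true effect only if EA beats sham, and it expressly declines to treat an EA v control win alone as one. Under that rule the efficacy error is 5%. The 12% counts sham v control, which the article nowhere proposes to test, and the 9% counts both directions. This stands as a limit on the size of the problem. It does not remove it, because the rule sits in the Discussion while Statistical methods and the sample size leave the contrast open.

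A second reply is that multiplicity handling is often left to a statistical analysis plan, which is not shown. That is fair for detail. But the article does fix a test and a threshold, and these cannot be applied to three arms without choosing a pair.

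On placebo, a reader might infer that any non-significant EA–sham result will be declared a placebo effect, and that false placebo conclusions are likely. The text does not support this. It also requires EA to beat control, it says only that placebo should be considered, and it admits that the trial may be inconclusive. A wholly false placebo reading needs an inert sham, where the pattern appears in only 10–14% of trials. The figures near 50% assume a sham effect that really exists. The error there is missing the specific part of the effect, not inventing a placebo part.

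Nor is 3.40 h established as the planning difference: the stated 29 comes from 3.73 h, and the article names neither.

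**Conclusion.** The point holds in a limited form. Statistical methods does not name the contrast that the Discussion treats as decisive. Followed literally, it carries a familywise error of about 12% over three pairs (about 9% over the two EA contrasts, both directions) instead of 5%, with no allowance in the sample size. It does not follow that false efficacy claims are likely: if EA v sham alone decides, the error is 5%.

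The placebo reading rests on non-significance, in a contrast whose power the article does not establish and whose 95% CI is about ±2.6 h. The triggering pattern occurs in about 10–14% of trials with an inert sham and about 50% if sham carries half the effect. These figures rest on 26 evaluable per arm, the source study's differences and SDs, normal data and assumed sham shares.

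**What to change.** In Statistical methods:
- name EA v sham as the single primary comparison, two-sided 0.05;
- test EA v control at 0.05 only if EA v sham is significant;
- report sham v control as an estimate with a 95% CI.

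In the Discussion, say that a non-significant EA v sham result is reported with its CI as inconclusive unless that CI excludes a pre-stated difference, and that a placebo effect is inferred from sham v control.

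In Sample size/recruitment, write down the pre-stated difference and say that the powered contrast is EA v sham.

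**Cost.** The change is wording and should be made before unblinding. Power for EA v sham is unaffected. EA v control becomes a formal claim only after EA v sham is won, although its estimate and CI are still reported. More results will be labelled inconclusive. For example, if 3.73 h were the stated difference, an observed EA–sham advantage between about 1.16 h (3.73 − 2.57) and 2.57 h would be neither significant nor enough to exclude it. The alternative of keeping all three contrasts as primary with a Bonferroni level of 0.0167 is dearer: power at 26 evaluable per arm falls from 81% to 67%, or enrolment rises to 37–38 per arm (111–114 in total).
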